# Towards patient-led follow-up after curative surgical resection of stage I, II and III colorectal cancer (DISTANCE-trial): a study protocol for a stepped-wedge cluster-randomised trial

**DOI:** 10.1186/s12885-023-11297-0

**Published:** 2023-09-07

**Keywords:** Follow-up studies, Colorectal neoplasms, Surveillance, Telemedicine, Aftercare

## Abstract

**Background:**

Colorectal cancer (CRC) is among the most frequently diagnosed cancers. Approximately 20–30% of stage I-III CRC patients develop a recurrent tumour or metastases after curative surgical resection. Post-operative follow-up is indicated for the first five years after curative surgical resection. As intensified follow-up after curative surgical resection has shown no effect on survival, patient organisations and policy makers have advocated for a more patient-centred approach to follow-up. The objective of this study is to successfully implement patient-led, home-based follow-up (PHFU) in six hospitals in The Netherlands, with as ultimate aim to come to a recommendation for a patient-centred follow-up schedule for stage I-III CRC patients treated with surgical resection with curative intent.

**Methods:**

This study is designed as a stepped-wedge cluster-randomised trial (SW-CRT) in six participating centres. During the trial, three centres will implement PHFU after six months; the other three centres will implement PHFU after 12 months of inclusion in the control group. Eligible patients are those with pT2-4N0M0 or pT1-4N1-2M0 CRC, who are 18 years or older and have been free of disease for 12 months after curative surgical resection. The studied intervention is PHFU, starting 12 months after curative resection. The in-hospital, standard-of-care follow-up currently implemented in the participating centres functions as the comparator. The proportion of patients who had contact with the hospital regarding CRC follow-up between 12–24 months after curative surgical resection is the primary endpoint of this study. Quality of life, fear of cancer recurrence, patient satisfaction, cost-effectiveness and survival are the secondary endpoints.

**Discussion:**

The results of this study will provide evidence on whether nationwide implementation of PHFU for CRC in The Netherlands will be successful in reducing contact between patient and health care provider. Comparison of PROMs between in-hospital follow-up and PHFU will be provided. Moreover, the cost-effectiveness of PHFU will be assessed.

**Trial registration:**

Dutch Trail Register (NTR): NL9266 (Registered on January 1st, 2021).

**Supplementary Information:**

The online version contains supplementary material available at 10.1186/s12885-023-11297-0.

## Background

Colorectal cancer (CRC) is the third most common cancer worldwide [1]. Approximately 12,000 patients are annually diagnosed with CRC in the Netherlands [2]. Over the years, overall survival (OS) of CRC patients has improved significantly due to earlier diagnosis, and improved treatment of the primary tumour and metastatic disease [3, 4]. After curative-intent surgical resection of the primary tumour, approximately 20–30% of stage I-III CRC patients develop a recurrent tumour or metastases [5–8]. A part of this group of patients with recurrent CRC can be treated curatively. The general assumption is that because early detection of recurrence leads to increased rates of curative treatment, [9] the OS of patients in follow-up will increase as well. However, intensified follow-up after curative surgical resection has not shown an effect on OS [10].

At present, surgically resected stage I-III CRC patients receive in-hospital follow-up for five years, and five-year relative survival for Dutch stage I-III CRC patients is 65–95% [11]. The follow-up conform Dutch guidelines encompasses a standard protocol for surgically resected stage I, II and III CRC patients with carcinoembryonic antigen (CEA) measurements every three to six months during the first two years, and every six to 12 months during the third, fourth and fifth year. A computed tomography (CT) scan of the thorax and the abdomen is indicated at 12 months after curative surgical resection [12]. The present follow-up guideline was presented in December 2020. Prior to this revision, CT scans and/or ultrasounds had a more prominent role in the CRC follow-up, combined with regular CEA measurements. The frequency of colonoscopies did not change.

A systematic review by Jeffery et al. focused on the different follow-up strategies for non-metastatic CRC patients, and showed that intensive follow-up was associated with fewer interval recurrences (relative risk [RR]: 0.59, 95% CI: 0.41; 0.86) and that the rate of salvage surgery increased with intensive follow-up (RR: 1.98, 95% CI: 1.53; 2.56). They however concluded that there is no evidence for OS benefit for intensified follow-up after curative surgical resection (hazard ratio: 0.91, 95% confidence interval [CI]: 0.80; 1.04) [10]. Several large randomised controlled trials were included in this systematic review, such as the CEAwatch trial, [13] the FACS trial, [14] the COLOFOL trial, [15] and the GILDA trial [16]. Combined, abovementioned studies have provided the scientific basis for the present Dutch guideline on CEA-guided follow-up for curatively treated stage I-III CRC patients.

A narrative review by Qaderi et al. showed that hospital-based CRC follow-up is common and associated with high patient satisfaction, but that there is also a willingness of patients and health care providers for alternative CRC follow-up, including general practitioner-led or patient-led, home-based follow-up (PHFU) [17]. Qaderi et al. studied the implementation of such a PHFU plan at the Radboud university medical center, Nijmegen, The Netherlands [18]. One year after implementation, no statistically significant differences in health-related quality of life (HRQoL) or fear of cancer recurrence were found. Patient satisfaction with the PHFU plan was rated with a mean of 7.5 out of 10 (standard deviation: 1.3). Also, the PHFU showed a considerable cost-saving compared to the previous follow-up plan, i.e., a total cost of €14,880 versus €37,288 per year for the included patients (*N* = 118). Both studies by Qaderi et al. showed that there is a clear potential for PHFU. Accordingly, extension of scientific knowledge on this setting of CRC follow-up is desirable. This knowledge can be generated by means of an implementation trial of PHFU for CRC in a research setting.

This study aims to successfully implement PHFU for CRC in six hospitals in the Netherlands, and to evaluate the outcomes by making use of the infrastructure of the Prospective Dutch CRC cohort (PLCRC) [19, 20]. After diagnosis of CRC, patients can be informed about PLCRC and asked informed consent for the different components: use of medical data, and optionally questionnaires on patient reported outcome measures (PROMs), withdrawal of additional blood samples, participation in other (sub)studies and to be informed about coincidental findings.

The design of this study is a stepped-wedge cluster-randomised trial (SW-CRT). Patients will be followed between 12 and 24 months after curative surgical resection. Patient data collected in this period will be used to assess the study outcomes. The following outcomes will be compared between condition A and condition B: proportion of patients who had contact with the hospital regarding CRC follow-up during the study period, HRQoL, fear of cancer recurrence, anxiety, depression and distress, cost-effectiveness, and OS. Combined, these outcomes will determine the success of implementation. The final objective of this study is to come to a recommendation for a patient-centred follow-up schedule for stage I-III CRC patients treated with surgical resection with curative intent.

## Methods/design

### Study setting

The study will be conducted in six hospitals in The Netherlands. The participating centres have no previous experience with PHFU for CRC. Five hospitals are non-academic teaching hospitals (Bernhoven Hospital, Catharina Hospital, Gelre Hospitals, Jeroen Bosch Hospital, Rijnstate Hospital). One hospital is a university medical centre (University Medical Center Utrecht). The six participating centres act as clusters. The study features two conditions: condition A (in-hospital, standard-of-care follow-up) and condition B (PHFU). All six participating centres will start including patients in condition A. Three centres will perform the switch from condition A to condition B after six months of participation; the other three centres will perform the switch from condition A to condition B after 12 months of participation. The switch will be performed without a transition period. A graphical overview of the study design and setting is depicted in Fig. 1.

**Fig. 1 Fig1:**
[figure not shown]
DISTANCE-trial study design

### Eligibility criteria

All patients who underwent surgical resection with curative intent for pT2-4N0M0 (i.e., stage I-II) or pT1-4N1-2M0 (i.e., stage III) CRC in one of the six participating centres and who are disease-free at 12 months after curative resection are eligible for inclusion. Patients with pT1N0M0 CRC are not part of the study population, as oncological follow-up is not required for these patients, according to the current guideline [21] .

#### Inclusion criteria

In order to be eligible to participate in this study, a subject must meet all of the following criteria:Patient has pT2-4N0M0 or pT1-4N1-2M0 colorectal carcinoma treated with surgical resection with curative intent;Patient is aged ≥ 18 years;Patient gave informed consent for PLCRC;Patient is disease-free at 12 months after resection; andPatient will receive follow-up in the participating center beyond 12 months after resection.

#### Exclusion criteria

A potential subject who meets any of the following criteria will be excluded from participation in this study:Patient has macroscopically incomplete resections (R2);Patient needs in-hospital follow-up longer than 12 months postoperatively (e.g., patients with a severely complicated postoperative course, or patients enrolled in other studies that require in-hospital follow-up consultations); orPatient has confirmed hereditary CRC.

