### Interventions

After diagnosis of CRC, patients can be informed and included in PLCRC. If a patient gives informed consent, their PLCRC key study number is matched with their key number in the Netherlands Cancer Registry (NCR). PROMs are collected with questionnaires. PLCRC sends out these questionnaires at predefined time points from the moment of inclusion in PLCRC. For this study, specific questionnaires are added to the package of questionnaires to assess a possible difference in PROMs between condition A and condition B.

Prior to inclusion, patients have already received 12 months of follow-up care after their curative surgical resection. At the 12-month time-point, patients will undergo a diagnostic CT thorax-abdomen, colonoscopy and CEA measurement according to the current guideline. These results will be discussed at an outpatient clinic visit and will serve as baseline data for this study. This outpatient clinic visit will also be the start of the study for patients. Patients can still be included in PLCRC at this visit. According to the condition of the participating centre at the time of inclusion (A or B), a patient’s follow-up trajectory will differ corresponding to that condition.

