#### Patient-led, home-based follow-up (condition B)

Before or during their outpatient clinic visit at 12 months after curative surgical resection, patients who will receive follow-up under condition B will receive written information on the PHFU. The treating physician/nurse practitioner will educate the participant on the PHFU and consecutively start the PHFU. If patients are not eligible for PHFU, they will receive in-hospital follow-up.

Participants will have their blood samples for the CEA measurement drawn at their general practitioner, the local diagnostic laboratory or the hospital. Preferably, patients will have their blood samples drawn as close to home as possible.

In principle, participants will receive notification by (e-)mail or text-message that they will have to perform their blood sampling for the CEA measurement. Reminders will be sent when the patient has missed the CEA measurement.

The patient will evaluate their own CEA level through the online patient platform portraying their test results. If the CEA level is normal, the participant is instructed not to act. If the CEA level is abnormal or the participant experiences symptoms, the participant is instructed to seek contact with their treating physician/nurse practitioner. If the participant does not seek contact with their treating physician/nurse practitioner, but the treating physician/nurse practitioner notices an abnormal CEA level, the participant will be contacted. Due to this construction, abnormal CEA levels will always lead to contact between patient and the treating physician/nurse practitioner. This construction is visualised in Fig. 2. If a participant wants to plan an outpatient clinic visit, they can always contact their treating physician/nurse practitioner – even if their CEA levels are normal.

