#### Deviation from patient-led, home-based follow-up

After the centre has switched to condition B, PHFU is the new standard-of-care in a participating centre. For significant personal reasons, it is possible to deviate from PHFU and to provide the patient with the in-hospital, standard-of-care follow-up. Clear notation of the reason for the deviation needs to be documented in the electronic patient file of this patient. Patients who deviate from the condition of the participating centre but do meet the eligibility criteria, will be analysed following the intention-to-treat principle.

If a patient does not fit in the regular in-hospital follow-up at 12 months after curative surgical resection because of medical reasons, the patient meets an exclusion criterium and can therefore not be included in the study.

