### Recruitment

Around diagnosis, CRC patients are asked to be included in PLCRC by their treating physician. Patients can give their informed consent for different aspects of PLCRC (use of medical data, PROM questionnaires, additional blood samples, new studies, and information on diagnostic coincidence findings). One of the major advantages of PLCRC is that when patients have given their informed consent for PLCRC, they can participate in all studies that make use of the PLCRC infrastructure. During the outpatient clinic visit at 12 months after curative surgical resection, patients can still be recruited for and included in PLCRC.

Patients do not have a choice whether or not they are included in the in-hospital, standard of care follow-up or the PHFU; this is decided by the condition in which the participating centre is at the moment of inclusion. Once PHFU is implemented in a participating centre, this is the new standard of care for all CRC patients in follow-up in that centre. Only patients who are included in PLCRC, are eligible to be analysed in this study. Informed consent for this study specifically is not necessary.

Eligible patients are automatically included in this study. The principal investigator of the participating centre will keep track of the patients who are included in the study.

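### Eligibility is settled after the hospital's condition is known, and three sections give no single answer on who stays in the condition B analysis, so B can lose complicated patients selectively, mainly affecting PROMs and costs

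*Protocol article*

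**What the plan says.** All references are to the Protocol article.

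- **Exclusion criteria.** A patient is excluded under the rule "Patient needs in-hospital follow-up longer than 12 months postoperatively". Two examples follow, a severely complicated postoperative course and enrolment in another study that requires in-hospital visits. They are given as examples, so the list is open.
- **Interventions.** On the 12-month visit: "This outpatient clinic visit will also be the start of the study for patients". On consent: "Patients can still be included in PLCRC at this visit".
- **Interventions, condition B.** "If patients are not eligible for PHFU, they will receive in-hospital follow-up". The sentence concerns care and is silent on analysis.
- **Deviation from patient-led, home-based follow-up.** "Patients who deviate from the condition of the participating centre but do meet the eligibility criteria, will be analysed following the intention-to-treat principle". The same section words the medical exclusion differently, as not fitting regular in-hospital follow-up at 12 months.
- **Recruitment.** "Around diagnosis, CRC patients are asked to be included in PLCRC by their treating physician". Then "Only patients who are included in PLCRC, are eligible to be analysed in this study", and "Eligible patients are automatically included in this study". The local principal investigator keeps track of who is included.
- **Allocation of switch moment; Blinding.** Switch moments are randomised before inclusion starts, and blinding is stated to be impossible.

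**The concern.** In a stepped-wedge trial the comparison is fair only if the rule for entering the analysis works the same way before and after the switch. Here entry is settled after the hospital's condition is known, and partly by judgement.

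Under condition A every patient receives in-hospital follow-up. Deciding that a particular patient needs it changes nothing in that patient's care, and nothing prompts the decision. Under condition B the same decision determines whether PHFU can start, so it has to be made. Identical wording does not ensure identical application. If the decision also removes the patient from the trial, complicated patients could leave B while similar patients stay in A.

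PROMs and costs are at stake. A finding that PHFU leaves quality of life unharmed or saves money could partly reflect who was removed from B. Hospital and period effects in the mixed model cannot recover patients who are absent.

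**Working it through.** **1. One patient, three sections.** Take a patient judged at the 12-month visit in a condition B hospital to be unsuitable for PHFU.

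- Exclusion criteria: needs in-hospital follow-up beyond 12 months, so is out.
- Interventions, condition B: receives in-hospital follow-up. Whether the patient is analysed is not stated, and no PHFU eligibility rule separate from trial eligibility is given.
- Deviation section: stays in B by intention to treat, but only if eligible, which refers back to the first rule. Its own medical exclusion covers patients who do not fit regular in-hospital follow-up. A patient who needs in-hospital follow-up may fit it perfectly well.

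The three sections do not yield one answer. A similar patient in a condition A hospital would ordinarily just be included.

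**2. The plan's own figures.** 6 hospitals × 3 six-month periods × 20 patients = 360. Three hospitals run A-B-B and three run A-A-B, which gives 9 hospital-periods per condition, so 9 × 20 = 180 each. This reproduces the Sample size section. The same section expects contact in about 100% (A) and 40% (B), a difference of 60 points.

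**3. PROMs.** Let u be the share judged unsuitable and d their deficit against the other patients. The article gives neither, so both are assumptions. If they are removed from B only, A's mean includes them and B's does not:

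shift = u × d

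With d = 10 points on a 0–100 scale: u = 10% gives 1 point and u = 20% gives 2 points, in favour of PHFU. In standard-deviation units, with the deficit s measured against the overall mean, shift = u·s/(1 − u). For u = 10–20% and s = 0.5–1 this runs from 0.1 × 0.5/0.9 = 0.06 to 0.2 × 1/0.8 = 0.25 SD.

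**4. Primary outcome.** Assume unsuitable patients all have contact, A is at 100%, and 40% applies to those retained in B.

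- Dropped from B only: 100 − 40 = 60 points.
- Dropped from A and B: 100 − 40 = 60 points.
- Kept in both: B = u + 0.4(1 − u) = 0.4 + 0.6u, so the difference is 0.6 − 0.6u. For u = 5%, 10% and 20% this is 57, 54 and 48 points, lower by 3, 6 and 12.

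The first two lines agree, so differential exclusion adds no bias when A is at 100%. More generally, if contact among the other A patients is a, dropping from B only differs from dropping from both by u(1 − a). With a = 90% (assumed) that is 0.5, 1 and 2 points for the same u.

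The 3, 6 and 12 points are the effect of a broader target population. Reading 40% as the rate in all B patients does not alter this. Removal then gives (0.4 − u)/(1 − u) = 36.8%, 33.3% and 25.0% in B, differences of 63.2, 66.7 and 75.0 points, again the same whether A is trimmed or not.

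**5. Room for the fix.** At u = 20% the difference is 48 points, still above the 40 points used in the Sample size section. Recomputed power at 40 points, with ICC 0.20, a single hospital random effect as planned, and two-sided 5% and 4 degrees of freedom assumed, is 95.9% (100% against 60%) and 86.6% (70% against 30%).

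**The case against.** The case against is substantial, and much of it stands.

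- **The criterion is written once for all patients.** This stands. A reader might infer that it operates only under PHFU, but formally it also decides entry under A. Its two examples are largely facts known before the visit. What remains is that the list is open and that only B forces the decision.
- **Keeping non-PHFU patients in B is provided for.** Partly. The deviation section keeps eligible deviators, and Other variables records the centre's condition separately from participation in PHFU. The proviso on eligibility leaves the gap.
- **Late consent is weak evidence of bias.** This stands. Consent is normally sought around diagnosis, eligible patients enter automatically, and after the switch PHFU is standard care whether or not a patient joins PLCRC. Late consent is a residual route of unknown direction.
- **Covariate adjustment is planned.** This also stands in part. PROM models include patient and tumour characteristics, costs and QALYs are adjusted for baseline differences, and comorbidity is collected. Postoperative complications, which the exclusion names, are not in the article's list of other variables, so adjustment may reduce the imbalance without removing it.
- **The primary result would be inflated.** A reader might infer this from the 0.6u figure. It does not follow: with A near 100%, the contrast is 60 points whether these patients are dropped from B only or from both conditions.

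**Conclusion.** The concern holds as a risk created by the wording. Entry is settled after allocation by unblinded staff, through an open-ended criterion with practical consequence only under B, and intention to treat protects only patients already accepted as eligible. Condition B can be selectively depleted of complicated patients. It would go too far to say that B is enriched, since the article has no data on exclusions or late consents by condition.

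The size is modest and rests on assumptions: about 1–2 points on a 0–100 PROM scale if 10–20% are removed from B only and score 10 points worse. Costs are exposed in the same way, but the article gives no figure from which to size that. The primary contrast is hardly affected by differential exclusion. Keeping these patients in B would lower it by 0.6u, which is a change of target population. This is a cheap improvement; it does not undermine the design.

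**What to change.** 1. Reconcile the exclusion criterion, the condition B description and the deviation section, so that one rule states who is analysed.
2. Define the exclusion by a closed list of reasons documented before the 12-month visit, and apply it from records identically in A and B. Which reasons belong on the list is for the investigators.
3. Analyse under condition B every patient found unsuitable for PHFU at or after that visit. This concerns the analysis set only and changes no one's care.
4. Add a sensitivity analysis restricted to patients whose PLCRC consent predates the visit. It addresses the consent route, not the eligibility route.
5. Report exclusions and late consents by condition and recruitment period.

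The cost is eligibility wording, one extra analysis and one table. Centre condition, inclusion date and participation in PHFU are already collected; the PLCRC consent date should be available from that cohort. The primary effect may look slightly smaller, and the restricted analysis will have fewer patients. Inclusion began in July 2022, so new eligibility wording may not reach everyone. Exclusions already made would have to be re-checked from records where PLCRC consent exists, and the study-specific questionnaires may be missing for those patients.
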